**Secondary Outcomes**	

Pain, stiffness and physical function in past 48 hours	WOMAC Osteoarthritis Index – Likert version
Global perceived response to treatment for pain and for function	Ordinal scale (1-much worse, 2-slightly worse, 3-no change, 4-slightly better, 5-much better) at study completion
Health-related quality of life	Assessment of Quality of Life index (AQol)
Physical activity levels	• Physical Activity Scale for the Elderly (PASE) • Pedometer worn twice for one week

**Other measures**	

Compliance	• Daily hours of use recorded in log-book • 11 point horizontal numeric rating scale (end descriptors of 0 = not at all and 10 = completely as instructed) at study completion
Discomfort with insoles	• Assessed weekly in log-book on 5-point ordinal scale (1 = no discomfort, 2 = mild, 3 = moderate, 4 = severe, 5 = very severe discomfort) • 11 point horizontal rating scale (end descriptors of 0 = extremely comfortable and 10 = extremely uncomfortable) at study completion
Other adverse effects	Log-book and open probe questionning

Knee cartilage volume will be measured using magnetic resonance imaging (MRI). Knees will be imaged in a sagittal plane on a 1.5-T whole-body magnetic resonance unit (Signa Advantage HiSpeed GEMedical Systems, Milwaukee, WI, USA) using a commercial receive-only extremity coil. The following sequence and parameters will be used: a T_1_-weighted, fat-suppressed 3D gradient recall acquisition in the steady state; flip angle 55 degrees; repetition time 58 ms; echo time 12 ms; field of view 16 cm; 60 partitions; 512 (frequency direction, superior-inferior) × 512 (phase encoding direction, anterior-posterior) matrix; one acquisition, time 11 min 56 sec. Sagittal images will be obtained at a partition thickness of 1.5 mm and an in-plane resolution of 0.31 mm × 0.31 mm (512 × 512 pixels) [37]. Knee cartilage volume will be determined by a blinded assessor analyzing baseline and final MRI pairs. 3D image processing will be performed using the software program OSIRIS (University of Geneva). In this technique, the image data will be transferred to a workstation and an isotropic voxel size will then be obtained by a trilinear interpolation routine. The volume of individual cartilage plates will be isolated from the total volume by manually drawing disarticulation contours around the cartilage boundaries on a section-by-section basis. These data will then be resampled by means of bilinear and cubic interpolation (area of 312 × 312 μm and 1.5 mm thickness, continuous sections) for the final 3D rendering. The volume of the particular cartilage plate will then be determined by summing all the pertinent voxels within the resultant binary volume. The CV of this method in our hands is 2% [37]. Knee cartilage volume will be measured for both the medial and lateral tibial compartments but the primary outcome will be the change in medial tibial cartilage volume. Bone size is a significant determinant of knee cartilage volume and thus a potential confounder [38]. Medial and lateral tibial plateaux areas as a measure of bone size will determined by creating an isotropic volume from the sagittal, T1-weighted fat saturation images, described above. This data will be reformatted in the axial plane and the area directly measured from these images as previously described [19]. The CV for the tibial plateau areas is 2.3% [19].

A number of secondary outcomes will be used (Table 1). The Western Ontario and McMaster Universities (WOMAC) Osteoarthritis Index is a disease-specific instrument widely used in clinical trials, outcomes research and epidemiological surveys. Its validity, reliability and responsiveness have been demonstrated in an extensive range of studies [39]. The WOMAC consists of 24 questions covering pain, stiffness and physical function. It provides a total score as well as scores for each subscale.

The Assessment of Quality of Life (AQoL) instrument is designed to measure health-related quality of life. It has 15 questions that cover five dimensions including illness, independent living, social relationships, physical senses and psychological wellbeing. The AQoL has strong psychometric properties and is more responsive than other widely-used scales including the Medical Outcomes Study 36-Item Short Form (SF-36) [40,41]. It produces a single utility index that ranges from -0.04 (worst possible health-related quality of life) to 1.00 (full health-related quality of life). A clinically important difference in health related quality of life can be defined as a change of 0.04 AQoL units [42]. Population norms have been calculated for the Australian population [42].

Habitual physical activity will be measured in two ways, one using a questionnaire and the second using a pedometer. The Physical Activity Scale for the Elderly (PASE) will be used to measure both the level and type of recreational and occupational physical activity undertaken by participants over the previous week. The PASE was developed and validated in samples of older adults (age 55+ years) [43]. A pedometer (HJ-005 Omron Healthcare, Japan) will be worn at the waist for a week on two occasions, once at the beginning and once at the end of the 12-month study to record the number of steps taken per day. Participants will be asked to wear the pedometer full time during their waking hours. Pedometers have been found to be a simple and inexpensive means to estimate physical activity levels [44,45]. It is recommended that at least three days of sampling are needed to accurately assess activity levels given differences between weekends and weekdays [46].

Participants will rate their perceived change in pain and in physical function with treatment (compared to baseline) on an ordinal scale (1-much worse, 2-slightly worse, 3-no change, 4-slightly better, 5-much better). Scales of this kind are frequently used as an external criterion for comparison with changes in scores of other outcomes [47]. Measuring patient perceived improvement using a rating of change scale has been shown to be a clinically relevant and stable concept for interpreting truly meaningful improvements from the individual perspective [48].

A number of other measures will be obtained (Table 1). Participants will record compliance of and tolerance with both types of insoles in a daily log-book. They will record the number of hours per day of insole use. At the end of the 12 months, participants will also indicate their perceived compliance with the insoles using an 11 point horizontal rating scale with terminal descriptors of zero = not at all and 10 = completely as instructed. Discomfort with the insoles will be evaluated weekly in the logbook on a 5-point ordinal scale (1 = no discomfort, 2 = mild, 3 = moderate, 4 = severe, 5 = very severe discomfort) [28]. At the end of the 12 months, participants will also rate their overall level of discomfort of the insoles using an 11 point horizontal rating scale with terminal descriptors of zero = extremely comfortable and 10 = extremely uncomfortable. Other adverse effects and the use of co-intervention will be recorded in the log-book and by open-probe questioning by the assessor at trial completion. Log-books will be posted back to the assessor on a monthly basis and checked for completion.

### Sample size calculations

Our sample size of 200 ensures adequate power for the two principal endpoints of change in pain and change in knee cartilage volume. Assuming that lateral wedges result in a mean pain reduction of 2 on our numeric rating scale (the minimum clinically important difference to be detected in OA trials [49]), that control insoles have a small placebo effect of 0.5 and that there is a SD of change of 3 (based on our previous data evaluating conservative OA interventions [50,51]), 170 participants would be required in total to give 80% power (2 sided test, alpha = 0.05). We have previously demonstrated a reduction in pain of this magnitude with knee taping [50] and physiotherapy for knee OA [51].

The other major end point is rate of knee cartilage loss. We have previously shown that the rate of tibial cartilage loss is 5.3 +/- 5.2% per year in a cohort with knee OA [52]. We categorized OA participants into tertiles: cartilage loss <3% per annum, 3–8% per annum and > 8% per annum. We found a linear increase in the risk of undergoing a knee replacement within 4 years [53]. Participants who lost cartilage at the rate of 3–8% per annum had a 2.4 fold (0.4 to 12.2) increased risk of requiring a knee replacement compared to participants who lost cartilage at the rate of <3% per annum. Those with the highest rate of loss of knee cartilage (>8% per annum) had a 7.1 fold (1.4 to 36.5) increased risk of requiring a knee replacement. These data suggest that a clinically useful outcome with lateral wedges would be to reduce the rate of knee cartilage loss to <3% per annum. With 100 subjects in each arm of the study, we will have 80% power to show a difference between a 5.3 +/- 5.2% per year rate of cartilage loss in the control group [52] and a <3% rate of cartilage loss in the intervention group (2 sided test, alpha = 0.05). This also takes into account a 20% drop-out rate.

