### Statistical analysis

A blinded statistician will analyse the data. All analyses will be conducted on an intention-to-treat principle using all randomized participants. Missing data will be replaced by the last score carried forward. Demographic characteristics and baseline data will be summarised by descriptive statistics. For outcomes measured using an essentially continuous scale, differences in mean change from baseline to 12 months will be compared between groups using linear regression modelling adjusting for baseline levels of the outcome measure. For knee cartilage volume, bone area, age and gender will also be included as covariates [54,55]. Model assumptions will be checked by standard diagnostic plots [56]. Participant measures of perceived improvement following lateral wedges or flat insole treatments will be compared by calculating the relative risks and their 95% confidence intervals using log binomial regression [57].

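### The 170 participants stated for 80% power on pain is the 90% power figure; the protocol's own inputs need 126 to 128

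*Protocol article*

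**What the plan says.** All of the pain calculation is in the protocol article under Sample size calculations.

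- Effect in the wedge arm: "Assuming that lateral wedges result in a mean pain reduction of 2 on our numeric rating scale".
- Effect in the control arm: "that control insoles have a small placebo effect of 0.5".
- Variability: "there is a SD of change of 3", attributed to the group's earlier data.
- Result: "170 participants would be required in total to give 80% power (2 sided test, alpha = 0.05".

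The section opens with "Our sample size of 200 ensures adequate power for the two principal endpoints". The cartilage calculation follows in the next paragraph. It starts from "With 100 subjects in each arm of the study" and ends with the section's only mention of attrition: "This also takes into account a 20% drop-out rate". The pain sentence does not say whether 170 is a number randomised or a number with 12-month data.

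The Statistical analysis section analyses everyone randomised, by linear regression adjusted for the baseline value, and states: "Missing data will be replaced by the last score carried forward".

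**The concern.** The pain sentence prints every input that a two-sample calculation needs, so its result can be checked directly, and it does not follow from them. A gap of about a third is too large for rounding or for the choice between normal and t formulas. At least one of the four quantities (sample size, power, SD, difference) must therefore be misreported.

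Pain is a primary outcome, and anyone reading a null pain result will want to know what power the trial was planned to have. As written, the text offers 80% at 170, and the reader cannot tell which of the printed values to trust. The handling of drop-out adds to the difficulty: a rate is given beside one primary endpoint, while the other has a required number with no statement of whether attrition is included.

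**Working it through.** **Inputs** (Sample size calculations): difference δ = 2 − 0.5 = 1.5; SD of change σ = 3; two-sided α = 0.05; power 80%; equal arms (100 each); drop-out 20%. The standardised effect is 1.5 / 3 = 0.5.

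**Formula:** n per arm = 2 (z₁₋α/₂ + z_power)² (σ/δ)², with (σ/δ)² = (3/1.5)² = 4.

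**Attempt to reproduce 170 at the stated 80%**

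- 2 × (1.960 + 0.842)² × 4 = 62.8, so 63 per arm and 126 in total.
- The t-test gives 63.8, so 64 per arm and 128 in total.
- 170/128 = 1.33 and 170/126 = 1.35, so the printed figure is 33% to 35% too high. It does not reproduce.

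**What does give 170**

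- At 90% power: 2 × (1.960 + 1.282)² × 4 = 84.1, so 85 per arm and exactly 170. The t-test solution is 85.03 per arm.
- Power with 85 per arm is 90.3% (normal) or 90.0% (t-test).

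**Other routes tried on the stated difference and SD (normal approximation)**

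| Variant | Total |
|---|---|
| One-sided α = 0.05, 80% power | 100 |
| 85% power | 144 |
| 95% power | 208 |
| α = 0.025, 80% power | 154 |
| α = 0.01, 80% power | 188 |

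Leaving out the placebo effect (difference 2) gives 72. None of these is 170.

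**Drop-out**

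- Dividing by 0.8: 126/0.8 = 157.5, so 158; 128/0.8 = 160.
- Multiplying by 1.2 (a common slip): 152 to 154.
- If 170 were the number randomised and 20% were lost, 136 would remain (68 per arm), with power of 83.0% (normal) or 82.5% (t-test). That still does not give the stated 80%.

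**Power at the planned size**

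- 200 × 0.8 = 160 completers, 80 per arm. The normal approximation gives Φ(0.5 × √40 − 1.960) = Φ(1.202) = 88.5%; the t-test gives 88.2%.
- With all 200 observed, power is 94.2% (normal) or 94.0% (t-test).

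**Why 160 is the relevant completer count.** Take the cartilage assumptions as 5.3% against 3%, with SD 5.2. Then 2 × (1.960 + 0.842)² × (5.2/2.3)² gives 81 per arm, 162 in total. Power is 79.9% (normal) or 79.4% (t-test) at 80 per arm, but about 88% at 100 per arm. The cartilage claim of 80% therefore reproduces at 160 completers, in line with its 20% drop-out. The same people supply the pain data.

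**The case against.** The case for giving this little weight has several parts.

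- **The error is in the safe direction.** The sentence overstates the number needed. Cartilage is the more demanding endpoint and sets the sample size, so nothing in the design changes. This stands, and it limits the point to a correction of the text.
- **The figure might include an unreported drop-out allowance.** At 25% drop-out, 126 to 128 becomes 168 to 171. A rank test with efficiency 0.955 and 20% drop-out gives about 168. Neither is in the document, which states 20% drop-out and a linear regression. Adjustment for baseline would lower the requirement, not raise it. These routes show that the cause is uncertain, but they do not make the printed sentence correct.
- **A reader might infer that pain is under-powered, because 20% of 200 lost leaves 160, fewer than the 170 called required.** The documents do not support this. If the inputs are right, 170 is not the requirement for 80% power, and 160 completers exceed what is. The pain sentence does not say that 170 means completers; if it means randomised, 200 already exceeds it. Nor is 160 the number analysed: the plan analyses all 200, with missing scores carried forward. Carrying scores forward does not restore lost information, so 160 is a fair count of information, but it should be called completers.
- **A reader might suppose that a larger SD was used.** An SD of about 3.5 (3.47 by t-test, 3.49 by the normal formula) would make 170 fit 80% power, and 160 completers would then give about 77%. This is purely hypothetical: the value is solved backwards from 170 and appears nowhere in the document, which states 3.

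**Conclusion.** The point holds as an arithmetic error in a stated sample size and power for a primary endpoint. On the printed inputs 80% power needs 126 to 128 participants in total. The printed 170 is the 90% figure, and the stated drop-out does not account for the gap. A wrong power label is a plausible cause, but the text does not settle whether the power, the SD or the difference was misreported.

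It does not follow that the trial is too small for pain. On the stated inputs 160 completers give about 88% power, above the 80% claimed. That conclusion assumes that the SD of 3 and the difference of 1.5 are the values intended, that allocation is equal, that drop-out is 20% in each arm, and that the comparison is an unadjusted one of mean changes. The planned baseline adjustment would tend to raise the power. The article's condensed form does not excuse the error: the inputs and the result are both printed, and no fuller document could make that sentence true.

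**What to change.** Restate the pain sentence along these lines: with a difference of 1.5 and an SD of change of 3, 128 evaluable participants (160 randomised with 20% drop-out) give 80% power at a two-sided 5% level; 160 completers of 200 give about 88%.

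If a different power, SD or difference was in fact used to reach 170, give that value and the power that results at 160 completers. In either case, say whether the figure is before or after drop-out, and apply the same 20% to both primary endpoints.

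The cost is a corrected sentence and a check of the original calculation. The sample size of 200, the design and the analysis are unchanged.

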### Economic analysis

The economic analysis will be conducted from the perspective of the Australian health care system and the individual patient. Participants will record visits to health care providers (e.g. general practitioner, medical specialist, other health care professionals), prescription and over the counter medication, professional home care and hospitalization in a daily log-book. This will be completed and returned to the assessor on a monthly basis. The log-book will utilise a checklist format to minimize respondent burden and ensure high quality data with minimal data loss.

### Statistical analysis

A blinded statistician will analyse the data. All analyses will be conducted on an intention-to-treat principle using all randomized participants. Missing data will be replaced by the last score carried forward. Demographic characteristics and baseline data will be summarised by descriptive statistics. For outcomes measured using an essentially continuous scale, differences in mean change from baseline to 12 months will be compared between groups using linear regression modelling adjusting for baseline levels of the outcome measure. For knee cartilage volume, bone area, age and gender will also be included as covariates [54,55]. Model assumptions will be checked by standard diagnostic plots [56]. Participant measures of perceived improvement following lateral wedges or flat insole treatments will be compared by calculating the relative risks and their 95% confidence intervals using log binomial regression [57].

The primary economic evaluation will take the form of a cost effectiveness study with a range of outcome measures including the incremental cost per extra person with a clinically significant improvement in pain, per extra person perceived to be recovered, and per extra quality adjusted life years (using the AQoL over 12 months). A social perspective on costs will be taken that includes resource use incurred both by health services and by the participant irrespective of the source of payment. The inclusion of time/productivity gains is controversial and the cost effectiveness ratios will be calculated with and without these indirect costs. All health care costs will be included, however, to reduce the impact of extreme values, if inpatient hospital costs are unrelated to knee OA they will be excluded. Standard methods of economic evaluation alongside a clinical trial [58] will be used to evaluate the differences in resource use and health outcomes over 12 months between groups. The statistical analysis of costs data will be similar to outcome data although adjustments for overdispersion may be necessary. Confidence intervals for incremental cost effectiveness will be calculated directly using non-parametric bootstrapping [59]. In addition we will calculate a cost effectiveness acceptability curve based for a range of hypothetical money values of outcomes [60]. This will be done using individual cost and outcome data over the 12 months or, if adjustments for imbalance at baseline are necessary, using regression analysis [61]. Hypothetical money values will be taken from the decision making literature but the trial will also ask patients in each arm of the trial their willingness to pay for the treatment prior to and after treatment. This will not only provide money values for the calculation of net benefits but also provide evidence on the influence of health experience on the value of health outcome to patients.

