### Outcome assessment

Participants will be assessed at baseline and at 12 months by an assessor blinded to group allocation. Outcome measures have been selected based on those recommended for clinical trials of knee OA [35,36]. In those with bilateral knee OA, only the most symptomatic knee will be assessed.

Age, gender, duration of knee OA symptoms, previous treatment, surgery and medication use for knee OA will be obtained by questionnaire. Radiographic disease severity will be assessed from the baseline x-ray using the Kellgren and Lawrence grading system [31]. Skyline knee x-rays performed in nonweightbearing at 20° knee flexion will also be obtained to assess severity of OA within the patellofemoral joint. X-rays will be evaluated according to osteophytes and joint space narrowing based on a 4 point scale [34].

The primary outcomes will be knee pain and knee cartilage volume (Table 1). Average knee pain in the past week will be self-assessed by an 11-point horizontal numeric rating scale with terminal descriptors of zero = no pain and 10 = worst pain possible. Such measurement has demonstrated reliability in OA [35].

**Table 1 T1:** Outcome measures

**Primary Outcomes**	**Measurement**
Average pain in the past week	11 point horizontal numeric rating scale (end descriptors of 0 = no pain and 10 = worst pain possible)
Medial tibial compartment cartilage volume	Magnetic resonance imaging

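### With only baseline and 12-month assessments, carrying the last score forward gives every dropout zero change: both primary effects are diluted, and cartilage power at the planned 20% drop-out is about 75%, not 80%

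*Protocol article*

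**What the plan says.** All points are from the protocol article.

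- **Missing data** (Statistical analysis): "Missing data will be replaced by the last score carried forward". The sentence is general and exempts no outcome.
- **Analysis set** (Statistical analysis): "All analyses will be conducted on an intention-to-treat principle using all randomized participants".
- **Analysed quantity** (Statistical analysis): for continuous outcomes, "differences in mean change from baseline to 12 months will be compared between groups using linear regression modelling adjusting for baseline levels". Bone area, age and gender are added for cartilage volume.
- **Timing** (Outcome assessment): "Participants will be assessed at baseline and at 12 months by an assessor blinded to group allocation". For MRI the same section says "Knee cartilage volume will be determined by a blinded assessor analyzing baseline and final MRI pairs", so each participant has one scan at each end. The log-book records insole use, discomfort, adverse effects, co-interventions and health-care use. It does not record the pain score.
- **Power** (Sample size calculations): 100 per arm gives 80% power to separate a loss of 5.3% per year (SD 5.2) from a loss below 3%. The section adds: "This also takes into account a 20% drop-out rate".
- **Perceived change** (Table 1): "Ordinal scale (1-much worse, 2-slightly worse, 3-no change, 4-slightly better, 5-much better) at study completion".

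**The concern.** Carrying a score forward needs a score taken after baseline. Here there is none for either primary outcome, so the rule amounts to writing zero for the change of everyone without a 12-month value and then analysing those zeros as data.

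Four things follow.

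1. For a progressive structural measure, zero is not a neutral guess. The plan expects controls to lose 5.3% in a year and would call a loss below 3% a success, so a dropout from either arm is recorded as doing better than the success criterion.
2. The estimated treatment effect on both primary outcomes shrinks in proportion to drop-out.
3. The sample size paragraph and the analysis paragraph treat the same people differently. The first counts dropouts as lost, and the second keeps them in as zeros.
4. If drop-out differs between arms, a cartilage difference appears even when the insoles have no effect.

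For perceived change no earlier score exists at all, so the rule has nothing to carry.

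**Working it through.** **Inputs (Sample size calculations).** Cartilage: control loss 5.3, wedge loss 3 (the upper limit of the stated target), SD 5.2. Pain: improvement of 2 with wedges and 0.5 with control, SD of change 3. There are 100 per arm, drop-out is 20%, and alpha is 0.05 two-sided. Power is taken as Φ(difference/SE − 1.96).

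**Step 1: reproduce the stated cartilage power.** Remove the dropouts: 100 × 0.8 = 80 per arm.
- SE = 5.2 × √(2/80) = 0.822
- Power = Φ(2.3/0.822 − 1.96) = 79.9%

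This is the stated 80%, so the power statement assumes that dropouts are left out and the full 2.3-point difference is kept.

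**Step 2: apply the stated rule.** If a share d of an arm has change exactly 0 and the rest have mean m and SD s, then
- arm mean = (1 − d)m
- arm variance = (1 − d)s² + d(1 − d)m²

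Cartilage, d = 0.20 in both arms, 100 per arm:
- Means: 0.8 × 5.3 = 4.24 and 0.8 × 3 = 2.40, a difference of 1.84
- Variances: 0.8 × 27.04 + 0.16 × 28.09 = 26.13 and 0.8 × 27.04 + 0.16 × 9 = 23.07
- SE = √((26.13 + 23.07)/100) = 0.701
- Power = Φ(1.84/0.701 − 1.96) = 74.6% (simulation of 20,000 trials: 74.5%; with exactly 20 dropouts per arm: 76.2%)

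About 115 per arm would be needed for 80% under this rule.

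Pain, same rule:
- Difference: 0.8 × 2 − 0.8 × 0.5 = 1.20, down from 1.5
- Variances: 0.8 × 9 + 0.16 × 4 = 7.84 and 0.8 × 9 + 0.16 × 0.25 = 7.24
- SE = √((7.84 + 7.24)/100) = 0.388
- Power = Φ(1.20/0.388 − 1.96) = 87.1%

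**Step 3: sensitivity of the power figures under the rule.**

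| Drop-out, each arm | Cartilage (wedge loss 3%) | Pain (200 participants) |
|---|---|---|
| 10% | 81.9% | 91.2% |
| 15% | 78.4% | 89.3% |
| 20% | 74.6% | 87.1% |
| 25% | 70.6% | 84.5% |
| 30% | 66.4% | 81.6% |

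At 20% drop-out, cartilage power rises to 78.2% if the wedge loss is 2.9% and to 81.5% if it is 2.8%.

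**Step 4: unequal drop-out, no true effect (assumed splits).** Both arms truly lose 5.3%. With 25% missing in one arm and 15% in the other:
- False difference = 0.85 × 5.3 − 0.75 × 5.3 = 0.53 points, favouring the arm with more dropouts
- SE = √((26.57 + 25.55)/100) = 0.722
- Rejection in both tails = Φ(0.53/0.722 − 1.96) + Φ(−0.53/0.722 − 1.96) = 0.110 + 0.004, about 11% against a nominal 5%

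Swapping the arms reverses the sign and leaves the size unchanged. A 22%/18% split gives about 6%, and an equal split gives 5%.

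**The case against.** The mechanism is hard to dispute, but several stronger readings are tempting and go beyond the documents.

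- **Both primary outcomes lose their power.** They do not. Pain keeps about 87% with 200 participants at 20% drop-out, and about 81% even with 170. Only cartilage falls below 80%.
- **The cartilage shortfall is large or certain.** It is about 5 points at the plan's own inputs. A wedge loss of 3% is the least favourable reading of the target, and 2.8% or a drop-out of 10% takes power back above 80%. The calculation also ignores any precision gained from the planned covariates, whose size is not given. All this stands.
- **The rule flatters the wedge.** A reader might suppose that more wedge wearers leave because of discomfort. The documents do not say so. The Background reports greater compliance with wedges in an earlier trial. Someone who stops wearing the insole can also still attend at 12 months. The direction is unknown.
- **False positives on pain are inflated too.** With the same 25%/15% split, a rate of 8 to 9% appears only if both arms improve by 2 points. With the plan's control change of 0.5 in both arms, the false difference is 0.05 points and rejection is 5.2%, practically nominal.
- **Replaced knees drive the bias.** The article reports "Those with the highest rate of loss of knee cartilage (>8% per annum) had a 7.1 fold" the risk of replacement, but over 4 years and with an interval of 1.4 to 36.5. No 12-month rate is given, and advanced disease is excluded. This is a reason for a sensitivity analysis and does not size the bias.

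It can also be said that with equal drop-out the error is conservative. That is true of the test, but the estimate is still too small, and missing a real effect is a cost in a trial built to detect one.

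**Conclusion.** The point holds in limited form. The rule as written turns every missing 12-month value into zero change on both primary outcomes. For cartilage, that assumption contradicts the plan's own expected loss.

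At the planned 20% drop-out, equal in both arms and unrelated to outcome, each primary effect is diluted by 20% towards no difference. The stated 80% cartilage power does not match the stated analysis, which gives about 75% at a wedge loss of exactly 3% and equal SDs of 5.2. Pain power is not at risk.

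A false cartilage effect needs unequal drop-out. The 0.53 points and roughly 11% type I error depend on an assumed 10-point imbalance and could favour either arm. Separately, the rule is inoperable for perceived change.

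Because the rule is fixed in the text and determines both primary estimates, it should be changed before analysis.

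**What to change.** Replace the carry-forward sentence in Statistical analysis with the following.

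- **Primary analysis:** multiple imputation by arm, or a likelihood analysis of the observed 12-month values, under missing at random. Use the planned baseline-adjusted regression and, for cartilage, bone area, age and gender.
- **Sensitivity analyses:** at least one missing-not-at-random analysis for each primary outcome, with an explicit assumption for knees replaced during follow-up. Carried-forward values may stay here, labelled as such.
- **Perceived change:** a separate statement of how missing ratings are handled, since there is no earlier score.
- **Sample size paragraph:** state that the cartilage power refers to about 80 participants per arm with 12-month data, so that it agrees with the analysis.

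With two time points, these methods recover roughly the information in the completers, so cartilage power returns to about the stated 80% and pain is at about 88.5% (80 per arm). The cost is revised wording and a little more analysis work, with no added participants or visits. The downside is reliance on a missing-at-random assumption, which the sensitivity analyses are there to probe.
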